## Abstract

**Background:**

Social integration and mental health are vital aspects of healthy aging. However, close to half of Canadians older than 80 years report feeling socially isolated. Research has shown that social isolation leads to increased mortality and morbidity, and various interventions have been studied to alleviate loneliness among older adults. This proposal presents an evaluation of an intervention that provides one-on-one coaching, is intergenerational, provides both educational and socialization experiences, and increases technology literacy of older adults to overcome loneliness.

**Objective:**

This paper describes the protocol of a randomized, mixed-methods study that will take place in Ontario, Canada. The purpose of this study is to evaluate if an intergenerational technology literacy program can reduce social isolation and depression in older adults via quantitative and qualitative outcome measures.

**Methods:**

This study is a randomized, mixed-methods, feasibility trial with 2 conditions. Older adults in the intervention condition will receive 1 hour of weekly technological assistance to send an email to a family member, for 8 weeks, with the assistance of a volunteer. Participants in the control condition will not receive any intervention. The primary outcomes are loneliness, measured using the University of California, Los Angeles Loneliness Scale, and depression, measured using the Center for Epidemiologic Studies Depression scale, both of which are measured weekly. Secondary outcomes are quality of life, as assessed using the Older People’s Quality of Life-Brief version, and technological literacy, evaluated using the Computer Proficiency Questionnaire-12, both of which will be administered before and after the intervention. Semistructured interviews will be completed before and after the intervention to assess participants’ social connectedness, familiarity with technology, and their experience with the intervention. The study will be completed in a long-term care facility in Southwestern Ontario, Canada. Significance was set at *P*<.05.

**Results:**

This study was funded in April 2019 and ethical approval was obtained in August 2019. Recruitment for the study started in November 2019. The intervention began in February 2020 but was halted due to the COVID-19 pandemic. The trial will be restarted when safe. As of March 2020, 8 participants were recruited.

**Conclusions:**

Information and communication technology interventions have shown varying results in reducing loneliness and improving mental health among older adults. Few studies have examined the role of one-on-one coaching for older adults in addition to technology education in such interventions. Data from this study may have the potential to provide evidence for other groups to disseminate similar interventions in their respective communities.

**International Registered Report Identifier (IRRID):**

DERR1-10.2196/23767

## Introduction

Social integration and mental health are fundamental indicators of healthy aging and represent significant public health concerns among Canadian older adults. Unfortunately, up to 50% of the Canadians older than 80 years report feeling socially isolated [1]. Similarly, 10%-15% of the Canadian older adults living in the community experience depression, and 44% of older adults in residential care have a diagnosis of depression or symptoms of depression [2,3]. Social isolation has significant detrimental effects on older adults, and previous research has shown an association between loneliness and depression [4-6]. Social isolation and higher levels of depressive symptoms, in turn, uniquely and jointly, are associated with increased morbidity and mortality, including reduced quality of life, decreased mental health, cognition, and function, and increased hospitalizations [1,7-12].

Multiple factors have been posited to influence loneliness, including health factors such as chronic diseases, in addition to cognitive and functional decline that may lead to difficulties in communication and mobility [1,13,14]. Structural factors that affect social isolation include relocation and separation from family and friends [15]. Given the multidimensional nature of loneliness, preventing and reducing loneliness is a top priority in Canadian public health care policy [1].

Growing evidence supports the use of intergenerational programs in improving various indicators for both older adults and younger cohorts. Interventions to reduce loneliness and improve mental health in older adults have traditionally consisted of group-based and individual-based interventions [16-19]. These include support groups, outreach volunteers, and animal therapy. In addition, previous studies have investigated information and communication technology methods such as internet-based videoconferencing and the overall impact of internet usage to maintain contact with family and friends, with varying levels of efficacy [20-22]. Previous mixed-methods intervention studies have identified improvements in social behavior, social interaction, quality of life, and mood in older adults [23]. These studies include production of art (eg, puppets or music), group reading, and shared spaces to gather with loved ones and friends [24-27].

Quantitative evidence also supports the use of intergenerational programs with older adults and youth, demonstrating efficacy via measures in geriatric depression scales, life satisfaction scales, quality of life, and self-esteem scales [28-34]. Examples of such studies include electronic gaming, student volunteer programs, and reminiscence therapy [29,35,36]. However, given the inherent social support that underlies intergenerational programs, it would be expected that improvements in the outcomes above are potentially mediated by reductions in social isolation and loneliness. Despite this, few studies have examined the role of intergenerational programming via a mixed-methods approach to reduce social loneliness [37-40]. As such, programs of this nature serve to improve not only relationships between older adults and younger adults but also the technological literacy and connectivity of older adults to family and friends via the internet—a multi-modal strategy to reduce social isolation and loneliness.

Addressing perceived social isolation or loneliness by using technology requires that older adults have a certain level of information and communication technology literacy, which is defined as the ability to locate, evaluate, and communicate information using a digital platform [18]. However, many older adults have low information and communication technology literacy, yielding a “digital divide” between older adults and younger adults in Canada, wherein older adults are less likely to use the internet as compared to younger adults [41]. Previous research has shown that compared to other age groups, older adults have less confidence in using technology and often need support for setup and use [42]. To target this, the enTECH Computer Club (enTECH) was founded in 2015 at the University of Waterloo. enTECH student volunteers provide one-on-one education to support older adults living in long-term care homes to use technology to keep in contact with their families, stay connected to their communities, and generally browse the internet. This student club consists of around 30 student volunteers from the undergraduate to graduate level who volunteer to work in service retirement homes and long-term care facilities in Southern Ontario. enTECH presents an opportunity for intergenerational learning.

This study is being conducted to determine the feasibility and effects of the educational program of enTECH for older adults on the levels of loneliness and depression reported by older adults. We hypothesize that our intervention will reduce loneliness and depression in older adults.

## Methods

### Managing Stakeholders

The organization implementing the intervention is a student club affiliated with the student union at the University of Waterloo, Ontario, Canada. We received funding through an internal funding opportunity. In order to proceed with this study, permission was required from both the student union and the institution’s research ethics board. The student union acknowledged that they lacked the resources and infrastructure to host the study and study funds, and thus, they requested that study funding and logistics be managed exclusively by a research team. This delineation has made managing the study easier by eliminating redundant paperwork, thereby allowing finances to be managed by research staff experienced in the required procedures and documentation.

### Study Design

This study is a mixed-method, randomized feasibility trial with 2 conditions. Participants in the intervention condition will receive assistance in sending an email to a designated family member once a week. This program will be carried out by experienced enTECH volunteers who have been trained in teaching older adults how to use technology. Participants in the control condition will continue interacting with their family as they do now (ie, not via information and communication technology). Participants in the control group also have access to 3 public computers in the facility and recreational therapists if they require support.

### Inclusion and Exclusion Criteria

As the focus of this study is specifically older adults who do not currently communicate with their family members in text by using technology, this is one of the key factors when determining the eligibility to participate. Potential participants are asked to confirm that they do not currently contact their family members using technology, including email, text message/iMessage, or any other digital text-based messaging platform (eg, WhatsApp, WeChat, Facebook Messenger). No exclusion criteria on the basis of computer proficiency will be applied, as the club provides support to people, regardless of their computer skills.

As this study is asking older adults to communicate with family members, participants were asked, prior to the consent process, if they had a family member who would agree to respond to an email from them weekly. No contact information will be collected at this time. There are no age or physical ability requirements to participate in this study, as long as the potential participant resides in a long-term care home. There are no exclusion criteria based on previous information and communication technology experience or expertise. If a participant is unable to physically use the technology to send an email, a member of the research team will assist them with doing so. Staff at the location will be asked to both identify potential participants and residents of that location who may not be a good fit to participate. Participants will be excluded if they have cognitive impairment with the inability to consent. Participants who are unable to speak English will be excluded from this study.

### Ethics Approval

This study was approved by the University of Waterloo Office of Research Ethics as of September 2019. The study ID is ORE #41104.

### Randomization and Blinding

After the consenting process, participants will be randomized to either the intervention or the control group by using a computer-generated allocation sequence in a 1:1 ratio. If randomized to the intervention group, researchers will work with the participants to obtain a family member’s email address for use in the study. Owing to the nature of the study, participants cannot be blinded to allocation. Two separate research teams will facilitate the study. The clinical team will be carrying out the intervention, while the research team will be conducting the interviews and administering the scales. In order to maintain participant confidentiality and anonymity to the interviewers, participants will be assigned a participant ID number via the allocation sequence described above. This number will be known to both the clinical team and the research team; however, the research team will not be able to see the participants in the intervention group or those in the control group. When data are entered into the computer, the data will be associated with the participant IDs alone.

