#### Participant Recruitment

Participants will be recruited through a long-term care home in Southern Ontario. Recreational facilitators will assist in recruiting participants for the study. Moreover, brochures, pamphlets, and flyers (Multimedia Appendix 2) will be placed in the study location by the team, in addition to a town hall advertising the study. Potential participants will be asked 2 questions to determine eligibility: if they currently use email/texting/messaging to contact family members and if they believe a family member would be willing to respond to an email sent by them once a week (Multimedia Appendix 3). Collecting the contact information of the participants’ family members requires balancing of respect for the participants’ autonomy, along with their potential comfort with the study’s subject matter. After consenting, participants will be presented with 2 options so that the research team can contact their family members. One option will consist of the participant providing the research team with a ranked list of family members to potentially receive emails from the participant, along with their phone numbers. The other option will consist of providing the participants with an information sheet, written in layperson terms, which they can use to describe the study to the family members to ask if they would like to participate. Members of the research team will follow up after 3 days to see if the participants were able to contact their family members or to provide support to facilitate this contact. The research team will then offer to contact the family member on their behalf, and at such time will record the contact information of up to 3 family members and contact them using the telephone script (Multimedia Appendix 4). Recruitment for the study started in November 2019. We expected to enroll approximately 20 participants, 10 in each condition. We successfully enrolled 8 participants before the study was forced to halt due to the COVID-19 pandemic (Multimedia Appendix 5).

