### enTECH Intervention and Study Procedure

After obtaining informed consent, demographic information will be collected (Multimedia Appendix 6) and participants will be randomized as described above. The intervention outline is described below and detailed in the study flow chart of Figure 1.

*Week 0*: Members of the study team will conduct semistructured interviews with participants (Multimedia Appendix 7) and complete the Computer Proficiency Questionnaire-12 (CPQ-12) and the Older People’s Quality of Life-Brief version (OPQOL-Brief) questionnaire, which will be measured before and after the study period.

*Weeks 1-7:* Participants in the intervention group will complete the enTECH program. Trained enTECH volunteers will help older adults use either our laptops or participants’ own technology systems to email their family members. These sessions will take place in group settings in a public area in the long-term care facility accessible to all participants. Both the Center for Epidemiologic Studies Depression scale (CES-D) and the UCLA (University of California, Los Angeles) Loneliness Scale (version 3) will be measured each week in the intervention and control groups.

*Week 8:* Participants in both groups will complete their final session of the intervention, and they will then be asked to complete the CPQ-12, the OPQOL-Brief, the CES-D, and the UCLA loneliness scale. Participants in the intervention group will also be invited to complete a second interview discussing their experiences using technology to communicate with a family member (Multimedia Appendix 8).

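### Randomising before Week 0 and taking participant IDs from the allocation sequence leaves avoidable exposure; one equal-arm draw per start cohort after Week 0 would remove it cheaply

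*Protocol article*

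**What the plan says.** Randomization and Blinding gives the timing and the method: "After the consenting process, participants will be randomized to either the intervention or the control group by using a computer-generated allocation sequence in a 1:1" (allocation ratio). It adds that participants cannot be blinded. On labels it says: "participants will be assigned a participant ID number via the allocation sequence described above. This number will be known to both the clinical team and". Its other named party is the research team, although that team is not meant to see who is in which group.

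enTECH Intervention and Study Procedure begins: "After obtaining informed consent, demographic information will be collected". Randomisation is named in the same sentence, and the Week 0 interview, CPQ-12 and OPQOL-Brief come afterwards. On the setting it says: "These sessions will take place in group settings in a public area in the long-term care facility accessible to all participants".

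On selection, Inclusion and Exclusion Criteria says: "Staff at the location will be asked to both identify potential participants and residents of that location who may not be a good fit to" (that is, to take part). No criteria for a good fit are given. Participant Recruitment adds that the home's recreational facilitators help to recruit, and gives the target: "We expected to enroll approximately 20 participants, 10 in each condition". Eight had been enrolled when the trial stopped.

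On the interruption, the abstract says: "The intervention began in February 2020 but was halted due to the COVID-19 pandemic. The trial will be restarted when safe". The Results section expects recruitment to resume, subject to ethics board approval.

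**The concern.** Three features of the stated procedure give away protection that costs little to keep.

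- **Order.** As described, an unblinded resident can know the arm before giving the baseline OPQOL-Brief and CPQ-12 answers. Those answers feed the change scores compared under Secondary Outcomes.
- **Labels.** The ID is meant to keep interviewers unaware of the arm, yet it is issued from the list that determines the arm.
- **Selection.** Home staff apply a subjective filter in a building where intervention sessions can be seen. If they could also anticipate the next allocation, they could, without intending it, favour some residents for one arm. That bias enters before allocation, so the planned intent-to-treat analysis would not remove it.

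The restart is when selection matters most. New residents would be recruited after the programme has already visibly run.

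**Working it through.** **Inputs.** 1:1 ratio from a computer-generated sequence, type not named (Randomization and Blinding). About 20 participants, 10 per condition, 8 already enrolled (Participant Recruitment), so 20 − 8 = 12 remain. Planning effect 0.2 (Power). The selection shift *s* is not in the article; 0.25 and 0.5 SD are assumptions.

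**The article's own figure.** The 10 per condition has no derivation. It is half of 20 and is consistent with 1:1.

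**1. If a 10/10 list is enforced and all past allocations are known.** The guesser always names the arm with more places left. With *a* and *b* places left, the expected number of correct guesses is

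G(a,b) = max(a,b)/(a+b) + [a/(a+b)]·G(a−1,b) + [b/(a+b)]·G(a,b−1), with G(0,0) = 0.

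- Whole trial: G(10,10) = 12.34, and 12.34/20 = 61.7%.
- Last 12, averaged over the possible splits of the first 8: Σ C(8,k)·C(12,10−k)/C(20,10)·G(10−k,2+k) = 8.02, and 8.02/12 = 66.8%.
- If the first 8 split 4/4: 7.72/12 = 64%. If 6/2: 8.60/12 = 72%.
- Expected number of fully determined assignments at the end: 2×10/11 = 1.8.

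**2. Translation into bias.** Suppose each guess moves the chosen resident's score by *s* towards the guessed arm, with no shift when the arms are tied. The expected arm difference is then s × (correct − wrong)/10.

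| Guessing applies to | Correct − wrong | s = 0.25 SD | s = 0.5 SD |
|---|---|---|---|
| Last 12 only | 8.02 − 3.98 = 4.04 | 0.10 SD | 0.20 SD |
| All 20 | 12.34 − 7.66 = 4.68 | 0.12 SD | 0.23 SD |

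For scale, the standard error of a standardised difference at 10 per arm is √(2/10) = 0.45 SD.

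**3. If the list is unrestricted.** Guessing stays at 50%. P(exactly 10/10) = C(20,10)/2²⁰ = 0.176, and P(12/8 or more uneven) = 0.503. Efficiency at 12/8 relative to 10/10 is 4×8×12/20² = 0.96, a loss of 4%.

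**4. Small fixed blocks as a remedy.** With known blocks of 4, five blocks give 5 × G(2,2) = 5 × 2.83 = 14.17 correct guesses, or 70.8%. That is more predictable than a 10/10 list.

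**5. One draw for a whole cohort.** Every member is consented and measured before any member's arm exists, so no allocation within the batch can influence who enters it. The arms are equal, or differ by one if the batch is odd.

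**The case against.** A reader might infer that residents are allocated one by one against an enforced 10/10 quota, by people who know the earlier results. The article does not say so.

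- Randomising after consent also fits drawing a consented cohort together. Recruitment from November 2019 with a start in February 2020 fits that reading well.
- The list type and the concealment method are details that an article may leave to the full protocol.
- Sessions show who attends. They do not show the order of allocation or the places left, and before February 2020 they could show nothing.
- Nothing says that the restart continues the old list. The Gantt chart captions describe the first run as completed, which also fits a fresh start.
- Enrolling 8 residents between November and March does not suggest a surplus from which to choose.
- An ID taken from a sequence does not reveal the arm without the key, and the research team is not meant to see group membership.
- The 10/10 figure is an approximate expectation, so missing it contradicts nothing.

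All of this stands, and it rules out claiming that selection bias has occurred or is built in. Three things remain: the stated order of randomisation and Week 0, IDs tied to the sequence, and no stated arrangement for allocating new recruits at restart.

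**Conclusion.** This is a worthwhile improvement to the allocation procedure, not a demonstrated error. The order of steps and the source of the IDs are in the text and can be bettered whatever the list type.

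The 67% figure for the remaining 12 rests on three unstated conditions: one-at-a-time allocation, the remainder of a restricted 10/10 list, and knowledge of the first 8 arms together with the quota. The 0.10 to 0.20 SD range adds an assumed selection shift at every guess. Its upper end equals the planning effect of 0.2, yet it is under half a standard error at this sample size (0.20/0.45 = 0.45). It should be read as an illustration, not an estimate.

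A reader might also conclude that simple randomisation would fail the plan because 10/10 arises only 18% of the time. It would not, since a 12/8 split loses about 4% of efficiency.

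The feasibility label does not make the change pointless. Loneliness and depression are the named primary outcomes, tested at P<.05, and the trial is meant to guide a later randomised trial.

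**What to change.** Amend Randomization and Blinding and the opening of enTECH Intervention and Study Procedure, for example:

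*Residents consent and then complete the Week 0 interview, CPQ-12 and OPQOL-Brief shortly before the programme start. The whole start cohort is then randomised together, 1:1, in a single computer draw with equal arms, made by a person who does not recruit, deliver sessions or assess. Residents recruited after the restart form a separate batch with its own equal-arm draw. Participant IDs are numbered in consent order before the draw and are independent of the allocation sequence. The person making the draw keeps the key linking ID to arm.*

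If cohort allocation is already the practice, the change is mainly one of wording, order and IDs. It needs no extra participants or assessments, and resumption already depends on ethics board approval, so the pause is the time to make it.

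The costs are practical. Early consenters wait longer to learn their arm. Week 0 must fall close to the start so that baselines are not stale. Family email addresses for the intervention arm must be collected in a shorter window before Week 1.

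### The team that administers the scales is said not to see group membership, yet the protocol gives that team family-contact and email-help tasks that can reveal it

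*Protocol article*

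**What the plan says.** Under Randomization and Blinding, the article accepts that "participants cannot be blinded to allocation" and then divides the work: "The clinical team will be carrying out the intervention, while the research team will be conducting the interviews and administering the scales". Both teams know the participant ID, but "the research team will not be able to see the participants in the intervention group or those in the control group".

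Three other statements bear on this:

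- The same section makes one step specific to an arm: "If randomized to the intervention group, researchers will work with the participants to obtain a family member", the aim being that relative's email address. The staff are called only researchers.
- Participant Recruitment gives contact with families, after consent, to the research team. That team may receive a ranked list of relatives with telephone numbers. It checks on progress: "Members of the research team will follow up after 3 days to see if the participants were able to contact their family members". It may then record contact details and telephone the relatives itself.
- Inclusion and Exclusion Criteria covers participants whose physical limitations prevent them from emailing: "a member of the research team will assist them with doing so".

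The enTECH Intervention and Study Procedure section has the UCLA Loneliness Scale and the CES-D measured weekly in both groups in Weeks 1 to 7 and again in Week 8. After listing the Week 8 scales it adds: "Participants in the intervention group will also be invited to complete a second interview".

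**The concern.** Both primary outcomes (loneliness and depression) and both secondary outcomes (quality of life and computer proficiency) are questionnaires. The respondents know their arm, and the comparator is no intervention. Keeping the people who administer the scales unaware of allocation is therefore the only masking safeguard the design describes.

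If those people also arrange email contact for intervention participants, or sit with them to send emails, they learn the arm before or during the period in which the primary scales are collected. An assessor who knows the arm can affect how items are read out, prompted or clarified, in the direction the study hopes for. A later statement that assessors were unaware of allocation would then be inaccurate. The article presents the study as a guide to a future randomized trial, which could inherit the same division of tasks.

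**Working it through.** No arithmetic applies, because the point does not depend on alpha, power, effect size or sample size. The check sets the statements about staff roles beside the masking statement.

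1. **Which team is masked?** Randomization and Blinding identifies the research team as the staff who interview and administer the scales, and says they will not see who is in which group. The wording is loose. The heading, the preceding admission about participants and the two-team split make assessor masking the natural reading.

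2. **Family contact.** Participant Recruitment gives this to the research team and places it after consent, without naming an arm. Randomization and Blinding also places randomization after consent, and has the email address obtained only in the intervention arm, by staff whose team is not stated. Read together, the two sections describe a step that follows allocation, concerns intervention participants only and is carried out by the masked team. If contact were instead made for everyone, it would reveal nothing, but the two sections would then disagree about who is contacted. Either way the text needs reconciling.

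3. **Email help.** Only intervention participants send emails under the programme, so assisting with one reveals the arm. The help is given during the programme, alongside weekly administration of the UCLA scale and the CES-D. It is limited to participants who physically cannot send the email themselves. Such participants are foreseeable, since the criteria set no physical-ability requirement and the setting is a long-term care home.

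4. **Week 8 interview.** The research team conducts the interviews, and the second interview is for the intervention group only, so it does reveal the arm. It is listed after the final scales, and the outcomes section places it after the study has concluded. If that order is kept, knowledge gained there comes too late to affect that participant's recorded scores.

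5. **Participant ID and location.** IDs are given as follows: "participants will be assigned a participant ID number via the allocation sequence described above". This discloses the arm only if the number encodes it, which the article does not say. Sessions are held in a public area, but nothing places the assessors there.

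Steps 2 and 3 carry the point. Step 4 is minor, and step 5 shows no unmasking.

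**The case against.** The strongest reply is that research team is a loose label. Randomization and Blinding introduces both groups of staff as research teams, and elsewhere the term covers those managing funds and logistics. On that reading, the people telephoning families or helping with emails could be clinical-team members, and no sentence says outright that scale administrators do these tasks. Family contact is not expressly ordered after allocation, email help may concern few participants or none, and trained volunteers run the sessions. The stated purpose of the ID arrangement is confidentiality and anonymity to the interviewers, and the article never uses the phrase blinded assessor. Finally, self-report by unblinded participants leaves respondent bias whatever the assessor knows.

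Much of this stands, and it limits the point. A reader might infer that masking cannot hold at all, that every intervention participant is bound to be revealed, or that the ID numbers and the public sessions unmask people. The documents do not support these readings, because the label is ambiguous, the email help is conditional, the interview follows the scales, and neither the ID nor the location is shown to disclose anything.

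The contradiction itself remains. The section on blinding uses research team for the staff who give the scales, and the same term is then attached to tasks that can reveal the arm. Staff following the text as written would be exposed to allocation.

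**Conclusion.** The point holds in a limited form. As written, masking of those who administer the scales is contradicted for some, and possibly most, intervention participants, out of about 10 planned for that arm. Family contact is the wider route. Email help affects only those physically unable to send an email, and the article does not say how many that might be. The Week 8 interview is a minor route provided the listed order is kept.

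This rests on two assumptions: that research team means the same staff in all three sections, and that the family contact described under Participant Recruitment is the arm-specific step described under Randomization and Blinding. If either is wrong, the protocol needs clearer wording and the unmasking may be smaller.

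The document gives no basis for estimating the size of any bias in the UCLA or CES-D comparison. The change should be made because it is cheap and the trial is halted awaiting restart.

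**What to change.** Before the trial restarts:

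- Assign all family contact made after allocation, and all help with sending emails, to the clinical team. For family contact, the alternative is to make it for every participant after consent but before randomization, so that it carries no information about the arm.
- State explicitly that each participant completes all Week 8 scales before any intervention-only interview.
- Use one term for the staff who administer the scales and keep to it throughout.
- If the tasks cannot be separated, state plainly that assessors are not blinded.

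The cost is a change of wording and a small extra load on the clinical team, with no new staff. Contacting every family before randomization would mean approaching about 10 further families, those of the planned control group (20 − 10 = 10). The benefit is bounded: respondents still know their arm and report their own outcomes, so only the assessor's contribution to bias is removed.
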